**Discussion:**

This study will identify the efficacy and provide preliminary data on the possible mechanism of acupuncture in treating aMCI. Furthermore, it will also identify biomarkers of the gut microbiota, inflammatory cytokines, and brain function correlated with therapeutic effects. The results of this study will be published in peer-reviewed journals.

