#### Changes in gut microbiota

3.8.3.

Faecal samples of all patients will be collected at the beginning and end of the intervention. In the morning, participants will be requested to collect mid-medial faecal samples (at least 2 g) using a disposable stool kit. After the samples are obtained, they will be stored at − 20°C freezers, sent to the laboratory, and placed in the refrigerator at −80°C within 24 h for preservation. We will use a metagenomic sequencing technique to determine the gut microbiota of participants. The DNA of gut microbiota from faecal samples will be extracted using the kit. Subsequently, we will establish a DNA library (paired-end; insert length 350 bp of each sample) according to the manufacturer instructions of Illumina, and conduct high-throughput sequencing using paired-end readings of length 2 × 100 bp. Subsequently, cluster analysis, assembly and annotation of metagenomic data will be conducted. Finally, the annotation, composition, differences, and comparison of species in the intestinal microbiota of patients will be analysed, and the similarities and differences in the diversity and abundance of gut flora will be compared between the AG and WG.

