#### Expression of inflammatory cytokines

3.8.4.

Fasting blood samples of all patients will be collected at the beginning and end of the intervention. After obtaining the samples, a serum sample from the participants will be collected using sterile storage tubes; next, we will weigh 500 μL serum sample per tube using a sterilised centrifuge tube, and obtain multiple tubes of each sample for backup. The collected sample will be stored at − 20°C freezers, sent to the laboratory, and placed in the refrigerator at − 80°C within 24 h. Human serum tumor necrosis factor-α (TNF-α), interleukin-1*β* (IL-1*β*), interleukin-4 (IL-4), interleukin-6 (IL-6), interleukin-10 (IL-10), interleukin-18 (IL-18), cyclooxygenase-1 (COX-1), and cyclooxygenase-2 (COX-2) enzyme-linked immunosorbent assay (ELISA) kit will be used for detection.

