### Statistical analysis

3.11.

Data analysis will be performed using IBM SPSS version 21.0 (IBM Corp, New York). All data of clinical symptom outcomes will be analysed according to the intention to treat population. The Chi-Square test/Fisher’s Exact test will be used to analyse and count data. Continuous variables as means ± standard deviation or median (± interquartile range), and categorical variables as the number and percentage of participants.

The measurement data includes various scale scores, indicators of brain function, DNA library of gut microbiota, and expression levels of inflammatory cytokines. After exploratory analyses, for variables with normal distribution, independent samples *t*-test will be used for inter-group comparison, and paired samples *t*-test will be used for intra-group comparison. The Mann–Whitney U test will be used for non-normal distributed variables. The correlation analysis between clinical efficacy, gut microbiota, inflammatory cytokines, and brain function will be conducted using multiple linear regression analysis. *p* < 0.05 will be considered the threshold for statistical significance.

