Additionally, strong evidence supports that neuroinflammation is key in chronic neurodegenerative disease progression (55), and the occurrence of MCI is closely related to the neuroinflammatory response. Neuroinflammation serves as a broad range of immune responses in the CNS with microglia and astrogliosis as its pathological markers (56), presented by elevated cytokines and inflammatory mediators, causing synaptic disturbances and neuritic dystrophy thus contributing to the initial cognitive decline (57). For example, increased basal production of pro-inflammatory cytokines (IL-1*β*, IL-6, and TNF-α) and decreased production of anti-inflammatory cytokines (IL-4 and IL-10) were observed in senescence-accelerated mouse models (58). TNF-α is a multi-potent, inflammatory cytokine that can induce apoptosis *via* receptor activation (55); TNF-α messenger ribonucleic acid levels are related to the degree of apoptosis in hippocampal neurons, which is closely related to cognition (55). IL-1*β* can upregulate the production of other pro-inflammatory cytokines, prostaglandins, and toxic mediators by initiating a vicious cycle of biochemical pathways (59). Moreover, COX-2 is an inflammatory molecule related to neurodegeneration and associated with synaptic functioning and memory formation, the expression of which is mainly observed in neurons (55). Researchers found that acupuncture reduces LPS, TNF-α and IL-1*β* concentration and regulates BBB disruption in animal models of AD by adjusting the gut microbiota (49). Therefore, the gut-brain axis may be the target for acupuncture treatment of aMCI.

Recently, increasing number of randomized clinical trial (36, 60, 61) have recruited healthy volunteers and determined the pathological features in the population of patients by comparing them with patients. Patients with MCI were reported to have altered levels of peripheral and cerebrospinal fluid inflammatory markers, abnormal cognitive-related brain network function, and distinct gut microbiota composition compared with healthy controls (62–64). In order to discover potential biomarkers associated with aMCI, in this study, healthy participants will be enrolled to assess fMRI, gut microbiota, and inflammatory cytokines, and the differences between patients with aMCI and healthy controls will be identified. The findings will help us to understand the gut-brain axis characteristics of patients with aMCI.

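### Section 3.11 sets one p < 0.05 threshold for fMRI, metagenomic and serum-marker tests with no multiplicity control stated, so the biomarker claims would lack error control

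*Protocol article*

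**What the plan says.** Section 3.11 of the protocol article puts four kinds of data into one class: "The measurement data includes various scale scores, indicators of brain function, DNA library of gut microbiota, and expression levels of inflammatory cytokines". For this class, where variables are normally distributed, "independent samples *t*-test will be used for inter-group comparison, and paired samples *t*-test will be used for intra-group comparison"; otherwise the Mann–Whitney test is used. The domains are then linked: "The correlation analysis between clinical efficacy, gut microbiota, inflammatory cytokines, and brain function will be conducted using multiple linear regression analysis". The section ends with one threshold on p for all of this: "0.05 will be considered the threshold for statistical significance". No Bonferroni, Holm, FDR, cluster-level or other correction is mentioned for any domain, in 3.11 or elsewhere.

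The measurements are wide. Section 3.8.3 states: "We will use a metagenomic sequencing technique to determine the gut microbiota of participants". Section 3.8.4 names eight serum markers (TNF-α, IL-1β, IL-4, IL-6, IL-10, IL-18, COX-1 and COX-2). Section 3.8.2 gives fMRI acquisition settings but not the features to be tested.

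On what will be concluded, the Discussion paragraph of the abstract says of the study that "it will also identify biomarkers of the gut microbiota, inflammatory cytokines, and brain function correlated with therapeutic effects". The main Discussion (section 4) is softer and introduces the healthy controls with the words "In order to discover potential biomarkers associated with aMCI".

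**The concern.** A 0.05 threshold limits the error of one test. Here it is the stated decision rule for families that may hold hundreds of taxa and, depending on the imaging analysis, thousands of voxels. Each family is examined over at least four contrasts: aMCI versus healthy, acupuncture versus waiting list, and before versus after within each arm. Cross-domain regressions come on top. A list of features that pass p < 0.05 in such a setting carries no stated limit on how many are false.

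This touches the second of the two objectives in section 2, the gut-brain mechanism, and the biomarker statement in the abstract. A reader of the results could not tell a real marker from one that passed by chance, and later studies might be built on the wrong ones.

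**Working it through.** The article states no family-wise, false-discovery or power figure, and section 3.5 sets the sample size by precedent. There is therefore no figure of the plan to reproduce beyond the threshold itself.

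**Inputs**
- Significance level 0.05 per test (3.11); sidedness is not stated, two-sided assumed.
- 20 participants each in the acupuncture, waiting-list and healthy groups (3.5).
- Eight serum markers (3.8.4).
- Number of taxa tested: not stated; assumed 100 to 500.
- BOLD voxel 3.8 × 3.8 × 4.4 mm (3.8.2). Brain volume of 1.0 to 1.4 litres and voxel-wise testing are both assumed.

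**Step 1: expected false positives per contrast if every feature is null** (number of tests × 0.05)
- Taxa: 100 × 0.05 = 5; 500 × 0.05 = 25.
- Voxels: 3.8 × 3.8 × 4.4 = 63.54 mm³. 1,000,000 / 63.54 ≈ 15,739 and 1,400,000 / 63.54 ≈ 22,035 voxels. Times 0.05, this is about 787 to 1,102.
- Serum markers: 8 × 0.05 = 0.4. Chance of at least one if independent: 1 − 0.95^8 = 0.337. Over four contrasts, 32 × 0.05 = 1.6 expected.

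Correlation between tests changes the chance of at least one false positive, but not the expected counts.

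**Step 2: are most hits false?** This depends on the share π of tested features that are real and on power. For 20 versus 20, the noncentral t distribution gives power of 0.338, 0.693 and 0.869 at d = 0.5, 0.8 and 1.0. The share of significant results that are false is (1 − π) × 0.05 / [(1 − π) × 0.05 + π × power]. For π = 5% and d = 0.8 this is 0.0475 / (0.0475 + 0.0347) = 58%. Both π and d are assumptions:

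| π | d = 0.5 | d = 0.8 | d = 1.0 |
|---|---|---|---|
| 1% | 94% | 88% | 85% |
| 5% | 74% | 58% | 52% |
| 10% | 57% | 39% | 34% |
| 20% | 37% | 22% | 19% |
| 50% | 13% | 7% | 5% |

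Half of the hits are false when π = 0.05 / (0.05 + power), that is 12.9%, 6.7% and 5.4% for the three effect sizes. With 40 aMCI patients against 20 healthy participants, the break-even values are 10.3%, 5.8% and 5.0%.

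**Step 3: what correction costs.** Bonferroni over eight serum markers tests each at 0.05 / 8 = 0.00625. At d = 0.8 with 20 versus 20, power falls from 0.69 to 0.37. The effect detectable with 80% power rises from d ≈ 0.91 to d ≈ 1.19.

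**The case against.** The strongest reply is that section 3.11 never calls the p-values unadjusted. A 0.05 level is also what one applies to corrected p-values, and a condensed article may leave the correction to a fuller plan. This reading is possible but strained: the section lists the data types, names the tests and applies the threshold to them directly. If a fuller plan does correct, the article misreports the rule and still needs a sentence.

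Second, the imaging analysis is not described. Section 3.11 speaks only of indicators of brain function, and section 3.8.2 gives only acquisition settings, so a voxel-wise analysis is not established. A region-based analysis would involve far fewer tests. The number of taxa is not given either. This stands: both counts are conditional.

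Third, much of the framing is already cautious. The abstract calls the mechanism data preliminary, section 3.1 and the opening of section 4 speak of exploring, and section 4 lists the small sample as a limitation. This also stands and lowers the weight of the point. It does not supply an error rate, and it leaves the abstract's biomarker sentence stronger than the rest of the article.

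A reader might go further and infer that the reported biomarkers will mostly be chance findings. The document does not support that. By step 2 it needs fewer than roughly 5 to 13% of tested features to be real, and neither that share nor an effect size is given. It is plausible for sparse taxa or voxels. It does not follow for eight markers named in advance, with 0.4 false positives expected per contrast.

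**Conclusion.** The point holds in a limited form. One 0.05 threshold, with no multiplicity control stated, governs fMRI, metagenomic and serum-marker tests over several contrasts, while the abstract promises biomarkers. Applied as written, it leaves those claims without error control. Many of the high-dimensional hits could be chance, and possibly most if real signals are sparse. The sizes in step 1 assume that no feature differs; those for taxa and voxels also rest on assumed feature counts and, for voxels, on an analysis that the article does not specify. For the serum markers the problem is real but small.

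A reader might also infer that the efficacy conclusion is at risk. It is not: section 3.7 names a single primary outcome, ADAS-cog change, and its comparison between arms at 0.05 needs no correction on this account. The weight is therefore moderate; it concerns the mechanistic results and how they are labelled.

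**What to change.** In section 3.11:
- Keep p < 0.05 for the primary comparison of ADAS-cog change between the acupuncture and waiting-list groups.
- For taxa and diversity indices, use Benjamini–Hochberg FDR at 5% within each contrast.
- For fMRI, state the unit of analysis. Use cluster-level family-wise correction for voxel-wise maps, or FDR over regions if region-based.
- For the eight serum markers, use Holm or FDR.
- Label all of these analyses exploratory.

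In the abstract, promise candidate biomarkers only, which matches the softer wording of the main Discussion.

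The cost is a few sentences and standard software options, settled before the data are analysed; recruitment, visits and sample size do not change. The real price is fewer results called significant and lower power per marker. Bonferroni over eight markers, with the loss shown in step 3, is a severe case; FDR usually costs less.

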## Discussion

4.

We proposed a randomised controlled trial to investigate whether acupuncture can exert therapeutic effects in aMCI. The relationship between clinical efficacy and the gut-brain axis will also be explored.

The gut-brain axis, which is composed of the gut microbiota, central nervous system (CNS), blood–brain barrier (BBB), and various cytokines, has a profound impact on the brain and has multiple effects on memory, mood and behaviour (48). The human gastrointestinal tract is home to diverse microbial community genomes known as the “gut microbiome”. Accumulated evidence indicates that gut microbiota dysbiosis plays a crucial role in the onset and progression of MCI (23). Contrarily, MCI can also cause changes in the diversity and abundance of intestinal microbiota *via* the gut-brain axis (49). Studies have found that the gut microbiota genera in patients with MCI were similar to that in patients with AD but differed from that in healthy controls, and the alteration of microbiomes was correlated with the clinical severity score (50). In gut microbiome dysbiosis, gut microbiota can generate neurotoxic substances like *lipopolysaccharide* (LPS) and *trimethylamine*, which trigger the immune cells residing in the brain and activate the immune system, leading to neuroinflammatory responses and causing heightened gut permeability (51, 52), thereby influencing BBB and brain function. Data suggest that patients with MCI express greater levels of LPS and pro-inflammatory cytokines in the blood compared to healthy participants (53, 54).

Additionally, strong evidence supports that neuroinflammation is key in chronic neurodegenerative disease progression (55), and the occurrence of MCI is closely related to the neuroinflammatory response. Neuroinflammation serves as a broad range of immune responses in the CNS with microglia and astrogliosis as its pathological markers (56), presented by elevated cytokines and inflammatory mediators, causing synaptic disturbances and neuritic dystrophy thus contributing to the initial cognitive decline (57). For example, increased basal production of pro-inflammatory cytokines (IL-1*β*, IL-6, and TNF-α) and decreased production of anti-inflammatory cytokines (IL-4 and IL-10) were observed in senescence-accelerated mouse models (58). TNF-α is a multi-potent, inflammatory cytokine that can induce apoptosis *via* receptor activation (55); TNF-α messenger ribonucleic acid levels are related to the degree of apoptosis in hippocampal neurons, which is closely related to cognition (55). IL-1*β* can upregulate the production of other pro-inflammatory cytokines, prostaglandins, and toxic mediators by initiating a vicious cycle of biochemical pathways (59). Moreover, COX-2 is an inflammatory molecule related to neurodegeneration and associated with synaptic functioning and memory formation, the expression of which is mainly observed in neurons (55). Researchers found that acupuncture reduces LPS, TNF-α and IL-1*β* concentration and regulates BBB disruption in animal models of AD by adjusting the gut microbiota (49). Therefore, the gut-brain axis may be the target for acupuncture treatment of aMCI.

Recently, increasing number of randomized clinical trial (36, 60, 61) have recruited healthy volunteers and determined the pathological features in the population of patients by comparing them with patients. Patients with MCI were reported to have altered levels of peripheral and cerebrospinal fluid inflammatory markers, abnormal cognitive-related brain network function, and distinct gut microbiota composition compared with healthy controls (62–64). In order to discover potential biomarkers associated with aMCI, in this study, healthy participants will be enrolled to assess fMRI, gut microbiota, and inflammatory cytokines, and the differences between patients with aMCI and healthy controls will be identified. The findings will help us to understand the gut-brain axis characteristics of patients with aMCI.

According to the theory of TCM, aMCI belongs to the “amnesia” category, caused by a deficiency of kidney essence and brain marrow. The brain is the marrow sea and the house of the original spirit. The heart stores the spirit and controls mental activities. When the original spirit is damaged, disease occurs. The GV 20 is an acupoint of the governor vessel which runs through the brain and is the most frequently used acupoint in the treatment of MCI (65). GV 24 is located at the anterior part of the frontal lobe and is closely related to memory and thinking. Studies (66, 67) have found that acupuncture at GV24 or GV20 based on the gut-brain axis can relieve gastrointestinal symptoms and regulate the gut microbiome. EX-HN 18 is an extraordinary acupoint for insomnia, associated with cognitive decline in older adults. Treatment of insomnia can help prevent cognitive decline during ageing (68, 69). HT 7 is a specific acupoint of the heart meridian, which can regulate the mind and emotion, research shows that later-life emotional disorder increase the risk of cognitive impairment (70), and the gut microbes are involved in the onset and development of mood disturbance (71). It has been discovered that the gut-brain axis may be the common target of TCM treatment for insomnia and emotional diseases (72, 73). Besides, mindful awareness practice can ameliorate cognitive impairment and modulate the gut microbiome (74). KI 3, an acupoint of the kidney meridian, has the effect of tonifying the kidney and thus nourishing the brain marrow. A Delphi expert consensus survey (75) recommended selecting acupoints on the heart and kidney meridian for cognitive impairment. Thus, the above acupoints were selected to treat aMCI in this study.

The protocol has some limitations. First, the patients and acupuncturists cannot be blinded due to the nature of the intervention. In order to minimise the performance and detection bias, allocation concealment will be conducted in this study, and outcome measures will be taken by an assessor blinded to group allocation and intervention. Second, a fixed acupuncture regimen is designed and will be used for every participant in the trial without syndrome differentiation, which may fail to show the full efficacy of acupuncture. Third, the sample size is relatively small. The potential limitations of this study may impact the results, which may lead to the need for future studies.

This is the first randomised trial to integrate acupuncture into the gut-brain axis in patients with aMCI. Brain function, gut flora, and neuroinflammatory cytokines are indicators of functioning of the gut-brain axis. The differences in the above indicators between patients with aMCI and healthy individuals will be identified to determine gut-brain interaction characteristics in patients with aMCI. Additionally, changes in these indicators between the AG and WG before and after treatment will also be investigated to illustrate the potential mechanism of acupuncture’s therapeutic effects on patients with aMCI. The main advantage of this study is the collection and evaluation of multifaceted data. We hypothesise that acupuncture therapy can improve clinical symptoms in patients with aMCI by regulating the gut-brain axis. If the hypothesis is proven, acupuncture therapy would not only serve as a novel alternative approach for treating aMCI, but also offer new information to further clarify the mechanism of the effects of acupuncture.

## Ethics statement

The local ethical committee of the Affiliated Hospital of Chengdu University of TCM has approved the study protocol (ethical approval number: 2022KL – 041).

